#### Implementation Measures

Quantitative process measures included number of unique veterans referred and enrolled, number of visits per veteran, total number of consults placed per veteran, and total number of GEC services received. We also conducted semistructured interviews at baseline and ongoing throughout the intervention period with key stakeholders (VA facility PACT providers and leadership, GEC leadership, GECDAC directors and staff, experts on VA peer support specialists, and national peers in the PACT implementation team). Detailed notes were taken on the interviews, and some of the interviews were audio recorded. The research team held ongoing periodic reflections [50] with the peers and study team to explore challenges and successful and unsuccessful strategies, as well as the peers’ perspective on their role as part of the clinical team [50]. In addition, study-specific questionnaires were used to collect data on satisfaction with the intervention as well as its feasibility and acceptability (Table 3).

### Data Analysis

We will use a quantitative-qualitative convergent mixed methods approach to evaluate P2P intervention outcomes. Specifically, we will use the reach, effectiveness, adoption, implementation, and maintenance (RE-AIM) framework to guide a formative process evaluation and assess the 5 key RE-AIM outcomes [51].

#### Quantitative Analysis

For our primary outcome, we will first calculate the difference in the number of primary care PACT outpatient encounters 6 months before and after enrollment for each participant in both intervention and comparison groups. An independent, 2-tailed, 2-sample *t* test will then be used to compare the means of the pre-post differences in the number of outpatient PACT encounters between intervention and comparison groups. The mean pre-post difference will be reported for each group with the corresponding SDs and 95% CIs. The folded F statistics will be evaluated to report either the pooled or Satterthwaite *P* value. We will calculate group-specific means and proportions for sociodemographic and clinical factors. At baseline, categorical variables will be compared between groups with the Pearson chi-square test or with the Fisher exact test for rare outcomes. The *t* test will be used to compare means across groups. *P* values will be reported, with lower values interpreted as more stable and less likely to be sporadic. All quantitative analyses will be performed using SAS 9.4 (SAS Institute Inc).

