### Matched Comparison Group

Veterans in the matched comparison group were identified from the HNHR list, similar to the method used to enroll veterans into the P2P intervention. Comparison group veterans did not receive any peer services before or during the study period as evidenced by CPRS chart reviews and use data provided by the GECDAC. Comparison group participants were matched with P2P intervention participants on age, care assessment need score [34], JEN Frailty Index [35], and Nosos score [36,37] from the HNHR list for the period during which the P2P participant was recruited. Veterans in the comparison group received care as usual.

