### Data Collection

#### Demographic and Clinical Measures

The study team collected demographic, clinical, and use data from the CPRS and GECDAC on age, sex, race and ethnicity, marital status, care assessment need score [34], JEN Frailty Index [35], Nosos score [36,37], service-connected eligibility, 2-year emergency room visits, urgent care visits and primary care visits, and diagnosed conditions and services used among both intervention and comparison group participants (Table 3).

**Table 3 table3:** Data collection.

Outcome measures						Description of measures		Data source		Schedule		
										Baseline		6 months

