### Limitations

As this is a nonrandomized study, the greatest challenge is the identification of an appropriate comparison group. We selected a matched comparison group from the same HNHR list from which the intervention participants were recruited to reduce selection bias. By selecting a matched comparison group that is similar according to a set of matching variables, we help to ensure that any observed differences in outcomes between the intervention and comparison groups can be more confidently attributed to the treatment itself, rather than other factors that may differ between the groups. The final sample size included 114 veterans: 38 (33.3%) P2P intervention participants and 76 (66.7%) matched comparison group participants. We made efforts to mitigate sample size limitations by including a 1:2 ratio of comparison group participants. In addition, the inclusion of referred patients may be deemed a deviation from the original protocol. However, the referred veterans will be assessed for comparable characteristics with veterans recruited from the HNHR list. Recent VA data demonstrate that using a combination of administrative data such as the HNHR list and clinician judgment is best suited for identifying patients for intensive care management interventions [54].

Safety precautions during the COVID-19 pandemic and home visits presented a potential risk for the intervention in terms of protection of the peers and the protection of older veterans with HNHR who are frail. The peers were trained by the home-based primary care team to make home visits and were trained on proper personal protective equipment use. Furthermore, peer use of remote care was limited by the access to, and willingness and ability to use, technology of the veteran with HNHR [55]. Peers used remote care where suitable. This aligns well with national VA priorities and stakeholder feedback.

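### The primary change score uses only the 6 months ending at enrollment, so a visit dip or spike specific to recruited or referred veterans would be counted as a P2P effect

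*Protocol article*

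**What the plan says.** **Outcome and test.** The Quantitative Analysis section of the protocol article takes the "difference in the number of primary care PACT outpatient encounters 6 months before and after enrollment for each participant" in both arms. A two-tailed t test will then "compare the means of the pre-post differences in the number of outpatient PACT encounters between intervention and comparison groups". It fixes no significance threshold; P values are to be reported "with lower values interpreted as more stable and less likely to be sporadic". It describes no earlier window and no adjustment for baseline encounters.

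**Entry to the intervention arm.** Under Recruitment and Enrollment, veterans enter through a peer's call, an opt-in letter, or referral by PACT clinicians, nurses or social workers. Under Eligibility Criteria, some referred veterans were not on the high-need, high-risk (HNHR) list.

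**Comparators.** Under Matched Comparison Group, these come from the HNHR list for the period in which the participant was recruited. They are "matched with P2P intervention participants on age, care assessment need score", JEN Frailty Index and Nosos score.

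**Earlier data.** Demographic and Clinical Measures lists "2-year emergency room visits, urgent care visits and primary care visits" for both groups. The clinical characteristics row of Table 3 gives a 2-year history for emergency room and urgent care only.

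**Interpretation.** Limitations says that with matching, observed differences "can be more confidently attributed to the treatment itself, rather than other factors that may differ between the groups".

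**The concern.** The planned contrast is a two-period difference in differences. It estimates a P2P effect only if both groups would have changed by the same amount without P2P.

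The sole baseline is the half-year that ends at enrollment. For intervention veterans, that is the half-year most exposed to whatever led to recruitment. A veteran who had lapsed from care may be approached or may opt in. A veteran with a recent illness and extra clinic contact may be referred by the same team whose encounters are the outcome. Comparators have no such event, and they are matched on age and risk scores, not on recent visits.

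Return to a usual visit rate would then enter the primary result. A temporary dip before enrollment would look like benefit; a temporary spike would hide a benefit or look like harm. A reader of the planned result could not tell these from an intervention effect.

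**Working it through.** **1. The article's own figures.** 38 × 2 = 76; 38 + 76 = 114; 38/114 = 33.3%. These reproduce. The sample size was set by feasibility, so there is no power figure to check.

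**2. Assumptions not in the documents.** Mean 3 encounters per 6 months; Poisson counts around a gamma-distributed personal rate; correlation r between windows of 0.3, 0.5 or 0.7; two-sided alpha 0.05; no true effect. Recruitment weight is exp(-b × recent count) with b = 0.1, 0.2 or -0.1. Odds per extra visit are therefore multiplied by 0.90, 0.82 or 1.11. Comparators are taken as unrelated to recent count. If the matched risk scores partly track recent visits, the sizes below shrink.

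**3. Size of the spurious difference.** In this model the expected later count, given recent count p, is 3 + r(p - 3). The spurious change is therefore

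(1 - r) × (3 - mean recent count among recruits).

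Example, r = 0.5 and b = 0.1. The gamma shape is k = 3(1 - r)/r = 3, and the count parameter is q = 3/(3 + k) = 0.5. Recruitment changes q to 0.5 × exp(-0.1) = 0.452, so the recruits' mean is 3 × 0.452/0.548 = 2.48. The spurious change is 0.5 × (3 - 2.48) = 0.26.

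Simulation of 38 vs 76 (4,000 runs per setting) gave:

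| r | b = -0.1 | b = 0.1 | b = 0.2 |
|---|---|---|---|
| 0.3 | -0.33 | +0.28 | +0.52 |
| 0.5 | -0.34 | +0.26 | +0.45 |
| 0.7 | -0.42 | +0.23 | +0.39 |

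Repeat runs agreed (absolute size 0.23 to 0.53).

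**4. False-positive rate.** The variance of an individual change is about 2 × 3 = 6, so its SD is 2.45. The standard error of the group difference is 2.45 × √(1/38 + 1/76) = 2.45 × 0.199 = 0.49. Spurious differences of 0.23 and 0.52 are thus 0.47 and 1.07 standard errors. The normal approximation gives rejection rates of about 8% and 19%; simulation gave about 8% to 20%. Without selection on recent visits, the bias was about 0 and rejection about 5%.

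**5. A second model, with a shift in the pre-window only.** Counts have mean 3 and gamma shape 2; the planned folded-F and t test procedure was used.

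| Pre-window shift | Bias (encounters) | Rejection |
|---|---|---|
| None | about 0 | 4.8% |
| Halved, everyone in both arms | about 0 | 4.8% |
| Halved, 25% of intervention arm | +0.38 | 12% |
| Halved, 50% of intervention arm | +0.75 | 33% |
| Doubled, 25% of intervention arm | -0.74 | 24% |
| Doubled, 50% of intervention arm | -1.51 | 68% |

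The halving rows follow 0.5 × 3 × share shifted; the doubling rows follow -3 × share, within simulation error. Only the part that differs between arms causes bias.

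**6. What the supporting analyses do in the model of steps 2 to 4.**
- Months -12 to -7 as baseline: bias at most about 0.02, rejection 4% to 6%.
- Post count adjusted for the 6-month pre count: residual bias -0.009 to +0.012, rejection 3% to 6%.
- Change from months -12 to -7 to months -6 to -1: on average equal in size and opposite in sign to the spurious effect, but p < 0.05 in only 8% to 20% of biased runs.

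**The case against.** **A separate analysis plan may hold such checks.** Placebo windows and alternative baselines often sit there, and it is not shown. That stands as far as omission goes. The point here is directed at the primary comparison that the article does state.

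**The comparison group already protects the result.** A reader might infer that any dip or spike around recruitment appears as an effect. The documents do not support that: comparators are drawn for the same period, so shared changes, including pandemic ones, cancel. A reader might also infer that the result is biased. No encounter data show an arm-specific shift, and the selection strengths above are assumed.

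**An earlier window would not expose the problem in one trial.** Correct. The contrast between the two earlier windows is as imprecise as the primary one, and would usually miss a bias of this size. It also makes a poor gate. With no selection bias and a true effect of +1 encounter, it exceeded half the primary difference by chance in 32% to 34% of simulated trials.

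**Baseline adjustment may be enough.** In the selection model it removes the bias, so one cannot claim that only an earlier window helps. That model selects on the observed count itself. Selection on a temporary event that the count reflects only partly was not tested, which is a reason to report both analyses.

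**The article is cautious.** It is a feasibility pilot of a preliminary effect. Limitations calls finding a suitable comparison group the greatest challenge, plans to compare the characteristics of referred and listed veterans, and speaks of attributing differences with more confidence. It does not claim outright attribution. The planned comparison of characteristics, as described, does not look at the course of visits.

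**Conclusion.** The point holds in limited form. The stated primary contrast cannot separate a P2P effect from a return to usual visit rates that is specific to recruited or referred veterans, and the bias can run either way. Under the step 2 assumptions it is about 0.2 to 0.5 encounters, or roughly half to one standard error, with a false-positive rate of about 8% to 20%. A pre-window shift affecting a quarter or half of the intervention arm would give more, from about 0.4 to 1.5 encounters in the cases tried. These sizes depend on assumed counts and selection. What does not depend on them is that shared shifts cancel and arm-specific shifts do not. The sample size is unaffected. The article reports analysis as underway, so supporting analyses were still possible at that stage.

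**What to change.** Keep the primary comparison. First confirm that the 2-year primary care visits are available by date in both groups, and reconcile the Demographic and Clinical Measures text with Table 3. Then add, as supporting analyses:

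1. The same between-group comparison with months -12 to -7 before the index date as the baseline.
2. Post-enrollment encounters compared between groups, adjusted for the pre-enrollment 6-month count. This needs no earlier data.
3. The between-group difference in change from months -12 to -7 to months -6 to -1, with its 95% CI, as description and not as a pass/fail test.

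State that if these disagree materially with the primary result, it will be described as not separable from return to usual visit rates. Say whether the additions were made before or after outcome results were seen.

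**Cost.** One further window, if the visits are dated, and three estimates; no new participants or visits. The estimates will be imprecise: under the assumed counts the 95% CI for analysis 1 is about ±1.96 × 0.49 = ±0.95 encounters. For early enrollees the earlier window is pre-pandemic (July to December 2019 for a July 2020 enrollment), which period-matched comparators share.

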### Study Design and Sample Size

This study uses a mixed methods (qualitative-quantitative convergent) design involving a nonrandomized 2-arm trial comparing the 6-month P2P intervention group with a 1:2 matched comparison group.

As this study is a pilot intervention, sample sizes were determined by what was deemed feasible within the available time frame and resources rather than power calculations. We aimed to recruit 35 veterans with HNHR or referred veterans for participation in the P2P intervention.

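### The comparison group is matched 1:2, but the primary t test treats the two groups as independent, so its between-group standard error and P value do not fit the design (a conservative error)

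*Protocol article*

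**What the plan says.** Study Design and Sample Size describes a nonrandomized two-arm trial "comparing the 6-month P2P intervention group with a 1:2 matched comparison group". Matched Comparison Group lists the matching variables as age, care assessment need score, JEN Frailty Index and Nosos score, with comparators taken "from the HNHR list for the period during which the P2P participant was recruited". Results gives 38 intervention and 76 comparison veterans, enrolled between July 2020 and March 2022.

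Quantitative Analysis (and the Abstract, more briefly) fixes the primary analysis. The first step is to "calculate the difference in the number of primary care PACT outpatient encounters 6 months before and after enrollment for each participant". The second is "An independent, 2-tailed, 2-sample" t "test will then be used to compare the means of the pre-post differences in the number of outpatient PACT encounters". On variance, it says: "The folded F statistics will be evaluated to report either the pooled or Satterthwaite" P value. On intervals, it says: "The mean pre-post difference will be reported for each group with the corresponding SDs and 95% CIs". No matched-set term and no covariate is named.

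On imbalance: "At baseline, categorical variables will be compared between groups with the Pearson chi-square test or with the Fisher exact test for rare outcomes", and means are compared by t test. Eligibility Criteria adds that veterans referred by PACT providers were enrolled even when they were not on the HNHR list. The comparators came from that list.

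**The concern.** The design ties each intervention veteran to two comparators of similar risk from the same recruitment period, which here also means a similar phase of the pandemic. The analysis then sets that structure aside. Both variance options, pooled and Satterthwaite, assume that the two groups are independent, so choosing between them by the folded F test does not help. The article states this test outright, so the matter is not a detail left to a fuller document.

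What is at stake is precision. The study was sized by feasibility, and the Limitations section presents the 1:2 ratio as a way to offset the small sample. A test that ignores the sets throws away whatever precision the matching bought.

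A second, smaller issue sits beside it. The pre-enrollment PACT count is not a matching variable, and the two groups were not drawn from quite the same source. A single unadjusted contrast gives no view of how much the result depends on that.

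**Working it through.** **Stated figures.** 38 × 2 = 76; 38 + 76 = 114; 38/114 = 33.3%; 76/114 = 66.7%. The sample reproduces exactly. There is no stated power, alpha, SD or correlation to reproduce.

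**Inputs.** 38 sets of 1 + 2 (article). Within-set correlation of the change scores, rho: assumed 0 to 0.3. Effect of 0.5 SD of the change score: assumed. Nominal two-sided 5%: assumed, since the article sets no threshold.

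**Standard errors.**
- Independent test: SD × √(1/38 + 1/76) = 0.199 SD.
- Set-based: the variance of a participant's change minus the mean of two comparators is SD² × [1 + (1 + rho)/2 − 2 rho] = 1.5 SD² (1 − rho). Over 38 sets the SE is SD × √(1.5/38) × √(1 − rho) = 0.199 SD × √(1 − rho).
- Ratio of independent to set-based: 1/√(1 − rho).

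**Type I error of the planned test.** 2 × [1 − Φ(1.96/√(1 − rho))] gives 3.9%, 2.8% and 1.9% at rho 0.1, 0.2 and 0.3. Simulation with 40,000 runs gives 4.0%, 2.7% and 2.1%. The set-based test holds about 5% throughout.

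| rho | SE ratio | Type I error, planned test (simulated) | Power at 0.5 SD, planned vs set-based (simulated) |
|---|---|---|---|
| 0 | 1.00 | about 5% | 70% vs 68% |
| 0.1 | 1.05 | 4.0% | 71% vs 73% |
| 0.2 | 1.12 | 2.7% | 73% vs 78% |
| 0.3 | 1.20 | 2.1% | 74% vs 83% |

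At rho = 0 the unrounded powers are 70.0% and 68.4%, a loss of about 1.5 points. It arises because the one-sample set test has 37 degrees of freedom instead of 112.

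**Which quantities are affected.** The overstatement applies to the between-group P value and to any CI for the difference. It does not apply to the per-group CIs that the article names. The intervention interval uses one veteran per set. The comparison mean has variance SD² (1 + rho)/76, so this mechanism does not widen its interval either.

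**Why a baseline-adjusted check is worth having.** Suppose the groups are exchangeable given the pre-period count, with pre-post slope b, equal SDs before and after, and a baseline gap of d0 SD. The change-score contrast then carries a bias of −(1 − b) × d0. The SD of the change is √(2(1 − b)).
- b = 0.7, d0 = 0.2: bias 0.06 SD in size; SE 0.775 × 0.199 = 0.154; type I error about 7%.
- b = 0.3, d0 = 0.4: bias 0.28 SD in size; SE 1.183 × 0.199 = 0.235; type I error about 22%.

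All of b, d0 and the exchangeability condition are assumptions. If the groups instead differ by a stable level of use, the change score has no such bias and the baseline-adjusted model is the biased one.

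**The case against.** The strongest reply is that the error is in the safe direction. With positive rho the planned test rejects too rarely, and with rho at zero it is essentially exact, so it cannot manufacture a positive finding. Rho must also be the correlation of change scores. Differencing has already removed stable risk-related levels, so 0.2 to 0.3 may be high, although shared calendar period could leave some correlation. This is also a pilot of preliminary effect with no set alpha, and P values are to be read on a continuum. All of that stands and limits the severity. It does not make the test fit the design, and a P value read on a continuum is still shifted.

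A reader might infer more than the article supports:
- **That no residual imbalance is removed.** The outcome is a within-person difference, so stable additive differences between groups cancel. Only imbalance tied to change over time remains.
- **That prior PACT use never enters the outcome analysis.** The pre-enrollment count is half of the primary outcome.
- **That the stated 95% CIs are too wide.** They are per-group, and no interval for the difference is named.
- **That a baseline-adjusted model must be primary.** In a nonrandomized comparison, that exchanges one untestable assumption for another.

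How baseline balance is displayed is a reporting preference and is not part of this point.

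**Conclusion.** The point holds in a limited form. The article builds a 1:2 matched comparison and fixes a primary test that ignores the sets. The between-group standard error is too large by about 5% to 20% for rho between 0.1 and 0.3. At rho 0.2 to 0.3 this costs about 5 to 9 points of power for a 0.5 SD effect. These sizes rest on the assumed rho and effect, on normally distributed changes in the simulation, and on 38 complete sets of three. The mismatch itself needs no assumption. It should be corrected, but it does not threaten the study with a false positive.

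Possible bias from differences in prior use or from referred veterans is a separate matter. The article gives no baseline gap or slope, so neither its size nor its presence can be established. It justifies a sensitivity analysis, not a change of primary estimand.

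**What to change.** 1. Keep each veteran's pre-post difference as the primary outcome. Compare groups with a linear mixed model that has a random effect for matched set. Alternatively, use a one-sample t test on each participant's change minus the mean change of the two matched comparators. With complete sets both give the same estimated difference, though their degrees of freedom differ. Name one in advance.
2. Report the between-group difference with its 95% CI, in addition to the per-group means.
3. If GEE clustered on set is preferred, apply a small-sample correction. With only 38 clusters, uncorrected robust standard errors gave a simulated type I error of about 6.0%.
4. Add a sensitivity analysis that regresses the post-enrollment count on group, pre-enrollment count and the matching variables, with the set effect. State that it and the change score rest on different assumptions in a nonrandomized comparison, so that disagreement between them is read as uncertainty.

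The cost is a few lines in the planned SAS software and no new data, because utilization and the matching scores are collected in both groups. The set identifiers must have been kept. If rho is zero, the one-sample set test gives up about 1.5 points of power.

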## Results

The P2P project was funded in October 2019. Study enrollment began in July 2020 and was completed in March 2022. Our sample size consists of 114 veterans: 38 (33.3%) P2P intervention participants and 76 (66.7%) matched comparison group participants. Data analysis is underway, and study findings are expected to be published in late 2023.

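### Choosing the primary P value by a folded-F pretest gives no practical gain over a fixed Satterthwaite test and slightly miscalibrates the P value when variances differ moderately

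*Protocol article*

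**What the plan says.** The Quantitative Analysis section of the protocol article defines the analysis variable per person: "we will first calculate the difference in the number of primary care PACT outpatient encounters 6 months before and after enrollment for each participant". The primary test is described as "An independent, 2-tailed, 2-sample" t test, used to "compare the means of the pre-post differences in the number of outpatient PACT encounters between intervention and comparison groups".

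The choice between its two versions is left to a variance test: "The folded F statistics will be evaluated to report either the pooled or Satterthwaite" P value. No cut-off for the folded F and no significance level for the primary test are given. On interpretation, P "values will be reported, with lower values interpreted as more stable and less likely to be sporadic". On estimation, "The mean pre-post difference will be reported for each group with the corresponding SDs and 95% CIs".

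The design is a "nonrandomized 2-arm trial comparing the 6-month P2P intervention group with a 1:2 matched comparison group" (Study Design and Sample Size), and the Results section gives the realised sizes: "38 (33.3%) P2P intervention participants and 76 (66.7%) matched comparison group participants". The sample size was set by feasibility, and the article gives no SD or effect size.

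**The concern.** The folded-F step is a stated rule, so it can be judged as written. It makes the primary P value the outcome of a two-stage procedure: test the variances, then test the means with whichever standard error the first test points to. The P value is then reported as if the second test had been fixed in advance.

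This matters more with unequal group sizes. With 38 against 76, the pooled standard error is too small when the smaller group is the more variable and too large when it is the less variable. The pretest is meant to guard against this, but at these sizes it often misses moderate differences in variance, and the pooled P value is then the one reported.

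The folded F also assumes normal data and reacts to tail weight, and differences of encounter counts may well be heavy-tailed. What is at stake is the calibration of the primary P value, and whether the pretest offers anything in return.

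**Working it through.** **Inputs from the article.** n = 38 and 76 (38 + 76 = 114; 38/114 = 33.3%; ratio 1:2, all consistent). Two-sided two-sample t test on individual pre-post differences. Pooled or Satterthwaite chosen by the folded F.

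**Assumptions, not in the article.** Test level 5%; pretest cut-off 5%, varied from 1% to 20%; SD ratio r = SD(P2P)/SD(comparison) from 0.7 to 1.5; no true difference in mean change; groups treated as independent, as the plan does. The effect of the matching was not examined. The plan states no design figure to reproduce.

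**Step 1: why pooling is off when r is not 1.** Set the comparison SD to 1.

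- True variance of the difference in means: r²/38 + 1/76.
- Expected pooled variance: [(37r² + 75)/112] × (1/38 + 1/76).
- r = 1.3: true 0.0576, pooled 0.0485, ratio 0.841; the pooled SE is √0.841 = 0.917 of what it should be.
- r = 0.8: true 0.0300, pooled 0.0348, ratio 1.159; the pooled SE is √1.159 = 1.077 times what it should be.

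Pooling is thus anti-conservative if P2P is the more variable group and conservative if it is the less variable.

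**Step 2: error rate of the planned rule.** Normal changes, 200,000 simulated trials per row, 5% pretest; all entries are percentages of trials.

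| r | Folded F significant | Always pooled | Always Satterthwaite | Planned rule | Pooled, given that F kept it |
|---|---|---|---|---|---|
| 0.7 | 67.7 | 2.8 | 4.9 | 4.5 | 3.1 |
| 0.8 | 31.9 | 3.5 | 4.9 | 4.3 | 3.7 |
| 1.0 | 5.0 | 5.0 | 5.0 | 5.0 | 5.0 |
| 1.25 | 36.3 | 6.9 | 5.1 | 5.9 | 7.2 |
| 1.3 | 47.0 | 7.3 | 5.1 | 5.9 | 7.7 |
| 1.5 | 82.0 | 8.5 | 5.1 | 5.4 | 9.5 |

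Repeat runs give 4.2% to 5.8% for the planned rule, the same within simulation error. With a 1% pretest the rule runs from 3.9% to 6.4%; with a 20% pretest, from 4.8% to 5.3%. The last column explains the mechanism but is not the error rate of the procedure, because it covers only trials in which pooling was kept.

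**Step 3: heavy tails.** Here both groups have the same distribution, so every folded-F rejection is false.

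- Symmetric count differences: the folded F rejects in about 13% to 30% of trials.
- Skewed changes: 20% to 45%.
- Tail weight drives this. A change with zero skewness and excess kurtosis 6 triggers the F test in 30.2% of trials, a skewed one with the same kurtosis in 29.6%.
- The final error of the two-stage rule in all these settings is 4.8% to 5.3%, because a false rejection only moves the analysis to Satterthwaite.

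**Step 4: skewness and unequal SDs together** (gamma changes). At r = 1.5 the planned rule gives 6.1% and fixed Satterthwaite 5.9%; at r = 1.3, 5.4% and 5.6%; at r = 0.7, both 4.9%. Here the two are practically equal.

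**Step 5: cost of dropping the pretest.** With equal variances and normal data, fixed Satterthwaite loses no more than about 0.4 points of power against the pooled test. For example, at an assumed standardised difference of 0.56 the simulated power is 79.6% against 79.9%.

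**The case against.** The strongest reply is that the effect is trivial and no declared standard is breached. The article sets no alpha, reads P values on a continuous scale and describes a feasibility-sized pilot. Both tests and the selector are named in advance, so the analyst has little discretion beyond the unstated cut-off. The pretest also does much of its job: it keeps the error far closer to 5% than always pooling would. All of this stands, and it limits the point to calibration of the P value.

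Three stronger readings are tempting, and the documents do not support them.

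- **That the rule inflates the error rate because the P2P group is the more variable.** No SD appears anywhere. The heterogeneity mentioned in the Discussion describes the high-need population, from which the comparison group is also drawn. If P2P is the less variable group, the rule is conservative.
- **That the folded F's over-rejection on count data corrupts the primary result.** It over-rejects, but the consequence is a switch to the valid test, and the final error hardly moves. The driver is tail weight, not skewness as such.
- **That no interval for the treatment effect is planned.** The article mentions intervals for each group and does not mention one for the difference. In a condensed article that is silence, not exclusion, and it carries no weight here.

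What the reply does not supply is a reason to keep the pretest.

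**Conclusion.** The point holds as a minor one. The planned rule makes the primary P value depend on a variance pretest that brings no practical benefit over a fixed Satterthwaite test. With normal data and moderately unequal variances it moves the type I error by up to about 1 point at a 5% pretest, and up to about 1.4 points (6.4% − 5%) at a 1% pretest, in a direction that cannot be known from the article. When variances are equal, the error is essentially nominal.

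These sizes rest on an assumed 5% test level, assumed pretest cut-offs, assumed SD ratios and independent groups. A shift of this size would not by itself alter how a nonrandomised pilot is read. The case for changing the rule is that the alternative is simpler, better calibrated under unequal variances, and nearly free.

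**What to change.** Delete the folded-F sentence. State that the primary comparison uses the unequal-variance (Satterthwaite) two-sample t test in all cases, and report the between-group difference in mean pre-post change with its Satterthwaite 95% CI, beside the group-specific summaries already planned. The interval follows directly from fixing the test.

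The cost is one sentence, no new data or software, and at most about 0.4 points of power if the variances are in fact equal. The Results section says that data analysis is underway, so the report should disclose the change and say whether it was made before the primary result was seen.
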